**Fig. 2 Fig2:**
[figure not shown]
Schematic of working memory, *n*-back tests that will be administered while wearing the functional near-infrared spectroscopy cap to examine task-related changes in cerebral blood flow. The numerical n-back tests will precede with a short training session with feedback. Then 3 blocks of 1, 2, and 3-back tests (each block repeated 3 times), with a 20-s fixation screen between each of the 3 blocks and instructions before each n-back. Examples of correct responses for each *n*-back are labeled as “Target.” Heart rate (HR) will be measured at the start of the first 1-back. ISI, interstimuli interval

### Outcome measures

Outcome measures will be collected immediately prior to and immediately after each experimental condition.

#### Cerebral blood flow

The primary outcome measure will be the changes in oxygenated hemoglobin (oxy-Hb) using a non-invasive multi-channel continuous wave fNIRS instrument (portable NIRSport, 8-8 system, with short-separation channels, NIRx Medizintechnik GmbH, Berlin, Germany). The optodes will be positioned over the prefrontal cortex, with data sampled at 7.81 Hz at wavelengths 750 nm and 820 nm, for oxy-Hb and deoxygenated hemoglobin (deoxy-Hb), respectively. The fNIRS cap has 8 LED light sources and 8 detectors placed according to the standard 10–20 system, with a source-detector separation distance of 3 cm (Additional file 2). The eighth detector is split into 8 detectors for the additional short-separation optodes with a distance of 0.8 cm from each source (NIRx Medizintechnik GmbH, Berlin, Germany) to account for superficial blood flow [43, 58]. We chose to measure cerebral blood flow in the prefrontal cortex region as working memory tasks (such as the n-back) predominately activate this region [59–61]. After dimming the lights, and headphones placed on the participant to minimize auditory distractions, system calibration will be performed before each assessment using NIRStar 15.2 software, and using the predefined montage; and the fNIRS signals will be visually quality checked and noted during data collection for motion artifacts or lost channels. Cerebral blood flow measures will be taken simultaneously while the participant performs 3 cognitive tasks of different workloads (numerical 1-, 2-, and 3-back tests). Our primary outcome variables will be changes in oxy-Hb between the 1-back and 2-back, and between the 1-back and 3-back tests. We will also record deoxy-Hb concentrations. The frontal border of the fNIRS cap will be placed about 2 cm above the nasion point and centered on the Cz, in order to capture prefrontal cortex blood flow changes. We chose to examine oxy-Hb because this signal has been previously shown to correlate with blood flow better than the deoxygenated signal [62], and is more highly correlated with the blood-oxygen-level-dependent (BOLD) fMRI signal [62, 63], although both will be reported.

#### fNIRS calibration and data processing

Changes in cerebral blood flow (oxy-Hb) will be assessed using the MATLAB-based software NIRS Brain AnalyzIR toolbox (https://github.com/huppertt/nirs-toolbox) [64]. The data will be predicted on a block design, which is characterized by alternating periods of activity and rest to facilitate the acquisition of the fNIRS signals. Each trial will be preceded by 20 s of rest. Raw voltage will be converted to optical density, then to hemoglobin concentrations according to the modified Beer-Lambert law. After, the hemodynamic response function will be detected using an autoregressive model-based algorithm to solve for the general linear model (GLM), which allows for residuals of the GLM to be at random [65]. This approach uses pre-whitening filters using autoregressive models and employs iterative reweighted least squares, taking into account serial correlations, motion artifacts, and simultaneous regression of the short-separation channels. Gaussian functions will be used with a set standard deviation and separation of means according to the timeframe of the n-back task for the temporal basis of the function. First level statistics will be performed between each source-detector pair between the baseline (1-back) and the task conditions (2- and 3-back). False discovery rate (FDR) correction using a Benjamini-Hochberg procedure will be employed to correct for multiple comparisons at a critical level of < 0.05. Then, second-level group statistics will be performed on the regression coefficients obtained from the first-level statistics. Region-of-interest (ROI) statistics will be carried out to derive averages over all channels.

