### Hypotheses

We hypothesize that:
Task-related increases in oxy-Hb will occur after the conditions involving physical activity breaks and will either stay the same or decrease after the prolonged sitting, and these changes will be significantly greater for the higher intensity break.Cognitive performance, specifically reaction time and accuracy on the n-back tests, will improve after the physically active conditions, but decrease or remain the same after the prolonged sitting condition. The changes will significantly differ between sitting with or without breaks of different intensities, such that more favorable changes will occur when the breaks are of higher intensity.There will be a correlation between changes in oxy-Hb and cognitive performance.Psychological factors, including cortisol-measured stress, and self-reported mood, alertness, and sleepiness, will improve after the physical activity break conditions, which will be significantly different from the prolonged sitting condition, where there will be no change.Arterial stiffness will be reduced after the physically active break conditions, and these changes will be different from the prolonged sitting condition, where no changes will occur or an increase will be observed.Changes in oxy-Hb will be mediated by changes in arterial stiffness.Baseline arterial stiffness will moderate the change in oxy-Hb and cognitive performance, such that there will be a more pronounced change in those with lower arterial stiffness.

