### Sample size

Studies with a similar design, and in children and youth are lacking. Thus, the sample size is based on studies of young and older adults. Using the data from these studies [18–20, 31, 77–79] software G*Power (Franz Faul, Universität Kiel, Germany, v 3.1.9.2) was used to calculate effect sizes. Effect sizes between 0.9 and 2.4 for the change in oxygenated hemoglobin were calculated, producing sample sizes between 6 and 13 participants (given an *α* = 0.05 and *β* = 0.8 assuming a two-tailed test). However, in order to have high enough variance within this age group, we will recruit 16 participants.

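### The article's only stated multiplicity correction falls, by its position, on first-level channel tests and cannot protect the group tests of two unranked primary variables

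*Protocol article*

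**What the plan says.** The section on fNIRS calibration and data processing sets out a sequence. First-level tests compare 2-back and 3-back with 1-back for each source-detector pair. The next sentence reads "False discovery rate (FDR) correction using a Benjamini-Hochberg procedure will be employed to correct for multiple comparisons", with a critical level below 0.05. After that: "Then, second-level group statistics will be performed on the regression coefficients obtained from the first-level statistics". ROI statistics then average over all channels.

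The section on cerebral blood flow defines the primary outcome: "Our primary outcome variables will be changes in oxy-Hb between the 1-back and 2-back, and between the 1-back and 3-back tests". Neither variable is ranked above the other, and the article does not say whether one or both must succeed.

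The primary research question asks how oxy-Hb changes over each 80-minute condition and whether those changes differ between conditions. The first hypothesis adds that "these changes will be significantly greater for the higher intensity break". The section on statistical methods plans mixed models for within-condition differences and for time-by-condition interactions, and names no correction there. The sample size section works with one test: "given an *α* = 0.05 and *β* = 0.8 assuming a two-tailed test".

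**The concern.** A correction at the first level acts on p-values from within one participant's recording. No conclusion about the break conditions is drawn from those p-values. What moves to the group level is the set of regression coefficients, and a Benjamini-Hochberg step does not alter a coefficient. Once channels are averaged into one ROI value, the channel multiplicity that FDR is meant for no longer exists.

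The multiplicity that remains is of another kind: two primary variables and three conditions. The article gives no rule for it. A report that follows the text could state that multiple comparisons were FDR-corrected while each group-level test was judged at 5%. Readers would take the primary result to be better protected than it is.

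This is more than silence on multiplicity. The article specifies a method, a threshold and, by its order, a level of analysis, and that level is not the one at which the trial's question is answered.

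**Working it through.** **Inputs.** From the article: three conditions; two primary variables; 16 participants ("we will recruit 16 participants"); two-sided alpha 0.05. The value labelled β = 0.8 is read as power 0.8. Assumed: effect sizes are standardised paired differences (dz), and pre-post changes have equal variance and equal correlation across conditions. The correlation ρ between the two primary variables is not given, so 0 to 0.9 is shown.

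**The article's own figure first.** It states "Effect sizes between 0.9 and 2.4 for the change in oxygenated hemoglobin were calculated", "producing sample sizes between 6 and 13 participants". A paired two-sided t-test at 0.05 with 80% power needs n = 12 at dz = 0.9 (power 81.0%) and n = 4 at dz = 2.4 (power 87.7%). The stated 13 and 6 are close but not exact; a dz of about 0.85 gives 13. The calculation is compatible with a single test at 0.05, with no allowance for a second primary variable.

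**Bounds by formula.** For k independent tests at 0.05, P(at least one false positive) = 1 − 0.95^k.
- k = 2 (one interaction test per variable): 1 − 0.9025 = 9.75%.
- k = 6 (2 variables × 3 pairwise contrasts): 1 − 0.7351 = 26.5%.

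The six contrasts are not independent, because three pairwise differences share three means and the two variables share the 1-back baseline. Simulation is therefore needed.

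**Simulation under no effect** (n = 16, 40,000 trials per setting):

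| ρ | Interaction only, 2 variables | Pairwise gated by interaction | Six pairwise, ungated |
|---|---|---|---|
| 0 | 9.5% | 9.4% | 23.3% |
| 0.5 | 9.1% | 9.0% | 21.5% |
| 0.7 | 8.5% | 8.5% | 20.5% |
| 0.9 | 7.0% | 6.9% | 17.5% |

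The last column uses paired t-tests with 15 df. With a pooled within-participant error (30 df) it is 22.6%, 21.2%, 19.3% and 16.5%.

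The gated column hardly differs from the interaction column. With the gate in place, practically all the excess over 5% comes from having two primary variables. Without it, most of the excess comes from the contrasts: for one variable alone, three ungated contrasts give about 12%.

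**Check of possible remedies.** Take one condition differing on the first variable and no effect on the second (n = 16, pooled error).
- Holm across the two interaction tests, with pairwise tests at the level each variable reached: familywise error 7.2% at ρ = 0 or 0.5, and 6.1% at ρ = 0.9. Alpha passes to the second variable while the first still has a true pairwise null to test.
- Fixed 0.025 per variable with the gated pairwise step: 4–5%.

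Within one variable the gate is sound with three conditions. If all three means are equal, the 2-df test protects. If not, at most one pairwise null can be true.

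**Sensitivity cost for a single paired contrast at n = 16.** Detectable dz at 80% power is 0.749 at alpha 0.05 and 0.843 at 0.025. At dz = 0.9, power falls from 92.0% to 85.3%.

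**The case against.** The strongest reply is that the plan already contains most of the protection needed. The statistical methods section plans a time-by-condition interaction, and with three conditions this is naturally one 2-df test per variable. A reader might infer from the hypotheses that all six pairwise contrasts will be tested at 5%, and that 17–23% is therefore the plan's error rate. The article does not support that: it never lists the contrasts and never gives a 5% level for the group tests. The intensity hypothesis implies some pairwise comparison but does not say it would be ungated. This part of the reply stands, and 17–23% is the upper end of a range. Adding the six within-condition tests to the family would also go beyond the text.

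A reader might also infer that the FDR step serves no purpose. That is too strong. The sentence names no level, so first level is the natural reading of the order and not an explicit statement. Exploratory analyses without ROI averages are planned, and a channel-wise correction could be useful there.

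Third, this is a journal article, and rules for condition contrasts are often left to an SAP. It cannot be said that the trial has no group-level rule, only that the article states none. Finally, the Discussion calls this the first study of its kind, needing confirmation by later ones, which lowers the stakes.

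None of this removes the central point. The one correction the article does specify does not reach the ROI-averaged group tests, and two unranked primary variables exceed 5% even on the most favourable reading.

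**Conclusion.** The point holds in limited form. By its place in the sequence, the FDR correction applies to first-level channel tests and cannot protect the group-level ROI comparison. The two primary variables have no stated hierarchy or error rule, and the pairwise comparisons implied by the intensity hypothesis have no stated gate. The false-positive risk for the primary result is about 7–10% if the interaction alone decides for each variable, and about 17–23% if six contrasts are tested ungated.

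These figures assume 16 complete participants, no true effect, normal data with equal variances and correlations across conditions, and ρ between 0 and 0.9. Severity: should be fixed. It bears on the primary conclusion, but wording alone settles it, and a rule may exist in a document that is not shown.

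**What to change.** State the following before the results are analysed.

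- Carry all first-level coefficients forward without thresholding.
- At group level, test the 2-df time-by-condition interaction for each primary variable at a fixed alpha of 0.025. Alternatively, name one variable as the single primary and test it at 0.05.
- Test the three pairwise condition contrasts for a variable, at that same level, only if its interaction test is significant.
- Do not use Holm across the variables unless alpha passes to the second only after every hypothesis of the first has been rejected.
- Report within-condition pre-post changes as estimates with confidence intervals.
- Apply channel-wise FDR to group-level channel maps, and say so.

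If a full protocol or SAP already contains such a rule, citing it and stating the level of the FDR step would be enough.

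The cost is analysis wording and a modest loss of sensitivity, with no new data or participants. For a single paired contrast, the detectable dz rises from about 0.75 to 0.84, still below 0.9, the smallest effect size in the sample size section. The figure for the 2-df test depends on the pattern of effects across the three conditions. Naming one primary variable avoids the loss from splitting alpha.

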#### Cognitive performance

Cognitive performance in working memory will be assessed using a computerized *n*-back test [66], consisting of the 1-, 2-, and 3-back tests administered simultaneously with fNIRS measures. Participants will be required to indicate (via a key press within 2 s from stimulus onset) whether the digit presented on the screen was the same digit as the digit presented 1 stimulus previously (1-back), 2 stimuli previously (2-back), or 3 stimuli previously (3-back). Each digit will be presented for 1.5 s at an interstimuli interval of 500 ms. The n-back tests were created using E-Prime 2.0 (Psychology Software Tools). In order to reduce practice effects, participants will perform a shorter version (2 blocks) of the cognitive tests at the familiarization session and prior to data collection on each experimental day. The outcome variables for cognitive performance will include average reaction time (ms) and accuracy (average number of correct responses) for each test across 3 blocks of 20 digit sequences (see Fig. 2). There will be a 20-s rest between each set of 3 blocks, involving staring at a dot on the screen while internally counting up from 0 to allow for a short period of cognitive rest after instructions are presented on the screen. Practice tests with feedback will be provided before each testing followed by the actual testing without feedback. A task-based baseline was chosen (1-back), as rest is dynamic across age, and not considered an equalizer in younger age [67].

#### Arterial stiffness and pulse wave velocity

Arterial stiffness (defined as augmentation index [AIx]) and pulse wave velocity (PWV) will be measured using a SphygmoCor XCEL PWA/PWV system (AtCor Medical, Sydney, NSW, Australia) [68]. The technology is non-invasive, reproducible, and accurate using the radial pressure waveform to calculate the aortic pressure waveform. The AIx can be derived from the aortic pressure waveform and is defined as the difference between the first and the second systolic peak. PWV is considered the gold standard method for assessing arterial stiffness. PWV is calculated by the formula: PWV (m/s) = distance between measurement location (m)/transit time (s) [69]. First, after 2 min supine rest, blood pressure and AIx will be determined. Then, the distance from the suprasternal notch to the carotid site, from the suprasternal notch to the femoral site (top of the leg cuff), and from the femoral pulse to the top of the leg cuff will be measured using a measuring tape. These distances will be subsequently used to calculate PWV. Three high fidelity pressure waveforms will be recorded using a carotid tonometer with a leg cuff to capture blood pressure waveforms at the carotid and femoral sites. The average of the three high-quality recordings will be used to determine PWV (m/s).

### Other measures

*Stress* will be measured using salivary cortisol concentrations. Saliva samples (collected during the first hour after waking up on test days, prior to breakfast, and before and after the 80-min intervention) will be centrifuged for 10 min at 4 °C at 2800 rpm, and subsequently frozen at − 80 °C. Concentrations will be measured using the ELISA kit Abcam, ab154996. Questionnaires on mood, alertness, and sleepiness that have been previously used in studies with adolescents will be filled-in while seated after fNIRS measurement and prior to the 2-min supine rest before the arterial stiffness measurement. *Mood* will be assessed using the Positive and Negative Affect Scale (PANAS) [70–72], which includes 10 positive and 10 negative affects. Participants will rate on a 5-point scale (very slightly/not at all; a little; moderately; quite a bit; extremely) the extent to which they experience that mood at the present moment. The positive affect adjectives include interested, excited, strong, enthusiastic, proud, alert, inspired, determined, attentive, and active. The negative mood adjectives include distressed, upset, hostile, irritable, scared, jittery, afraid, ashamed, guilty, and nervous. *Alertness* will be measured using a simple 10-cm visual analog scale (VAS) [73], going from “not at all” to “completely alert”. *Sleepiness* will be measured using the Karolinska Sleepiness Questionnaire (KSS) [74–76], where participants will rate on a 9-point Likert scale their current level of sleepiness going from “extremely alert” to “very sleepy, great effort to keep awake, fighting sleep”.

### Data management

All participants will be assigned a unique identifier in order to remain anonymous. All personal data will be stored in encrypted files with access restricted to study staff. Original paper files will be stored in secure, locked cabinets on site. All data will be entered electronically at GIH. Data entered will be double-checked for errors at the time of entry, and changes made will be documented. Additional detection will be performed through the statistical software. Data ranges and consistency checks will be performed for data integrity. No specific auditing procedures are planned for this trial.

### Sample size

Studies with a similar design, and in children and youth are lacking. Thus, the sample size is based on studies of young and older adults. Using the data from these studies [18–20, 31, 77–79] software G*Power (Franz Faul, Universität Kiel, Germany, v 3.1.9.2) was used to calculate effect sizes. Effect sizes between 0.9 and 2.4 for the change in oxygenated hemoglobin were calculated, producing sample sizes between 6 and 13 participants (given an *α* = 0.05 and *β* = 0.8 assuming a two-tailed test). However, in order to have high enough variance within this age group, we will recruit 16 participants.

### Statistical methods

Mixed effects models with subject as a random effect to assess within condition differences will be performed, and to examine time-by-condition interaction effects. Changes in arterial stiffness and PWV will be assessed in relation to cerebral blood flow changes in the mixed models.

Exploratory analyses will be performed excluding the short-separation regressors and ROI averages to compare to the main analyses.

Secondary outcomes (i.e., cognitive function, psychological factors, stress), will be assessed using mixed models, with the subject as a random effect, looking at both the within condition changes and the time-by-condition interaction effects. Correlational analyses will be performed to investigate the association between changes in cognitive function and cerebral blood flow if significant changes are seen. Maximum likelihood estimation will be used in the mixed models to handle missing data at random. Subsequent sensitivity analyses will be performed if necessary.

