**Methods:**

This is a protocol for a randomized crossover study that will recruit 16 adolescents (13–14 years old). Participants will undergo three different conditions in a randomized order, on three separate days, involving sitting 80 min with a different type of break every 17 min for 3 min. The breaks will consist of (1) seated social breaks, (2) simple resistance activities, and (3) step-up activities. Before and after the 80-min conditions, prefrontal cerebral blood flow changes will be measured using functional near-infrared spectroscopy (primary outcome), while performing working memory tasks (1-, 2-, and 3-back tests). Arterial stiffness (augmentation index and pulse wave velocity) and psychological factors will also be assessed pre and post the 80-min interventions.

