## Methods and design

### Trial design

A crossover randomized trial with three conditions will be carried out. All procedures will take place at the Swedish School of Sport and Health Sciences (GIH) in Stockholm, Sweden. Initially, each participant will attend a familiarization visit either at the laboratory at GIH with parental accompaniment or the researchers will visit the schools.

After the familiarization visit, participants will be assigned 3 experimental days for undergoing 3 different randomly ordered experimental conditions, each consisting of an 80-min sitting exposure. There will be a minimum washout period of 7 days between each visit [51, 52], to reduce carryover effects from the previous condition. Two participants will be tested simultaneously (with a 20-min gap between starting times) to increase efficiency and comfort for the participants. Participants will have a 24-h monitoring and standardization of their physical activity, sleep, and dinner prior to each experimental test day. Participants will receive compensation (600 SEK gift card) for their participation.

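### The stated mixed model has no term for the visit that each pre/post pair shares, which can cost power on the time-by-condition test; missing data are no reason to prefer maximum likelihood to REML

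*Protocol article*

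**What the plan says.** For the primary outcome, the Statistical methods section of the protocol article states: "Mixed effects models with subject as a random effect to assess within condition differences will be performed, and to examine time-by-condition interaction effects". Secondary outcomes "will be assessed using mixed models, with the subject as a random effect". On estimation it says: "Maximum likelihood estimation will be used in the mixed models to handle missing data at random". No visit-level term, residual covariance, REML or small-sample method is mentioned. The section does allow for sensitivity analyses if they prove necessary.

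The layout of the data is set elsewhere in the article:

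- Abstract, Methods: "Participants will undergo three different conditions in a randomized order, on three separate days".
- Trial design: "There will be a minimum washout period of 7 days between each visit".
- Outcome measures: "Outcome measures will be collected immediately prior to and immediately after each experimental condition".
- Sample size: "we will recruit 16 participants".

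Each participant therefore contributes six values per outcome, in three same-day pairs.

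**The concern.** A random intercept for subject, taken alone, makes any two values from one participant equally correlated, whether they were taken on the same morning or weeks apart. The article itself treats the state of the day as important: it monitors activity, sleep and diet for 24 hours before each visit and standardises breakfast. If values from one visit are more alike than values from different visits, that shared part cancels in the within-visit change. It does not cancel in the pooled residual that the subject-only model uses to test time by condition. The test of the primary question would then give up some of the precision that measuring before and after each condition was meant to provide.

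A second, smaller matter is the estimator. ML does not allow for the fixed effects when it estimates variances, so it gives values that are too low in small samples. The reason offered for it, data missing at random, applies equally to REML.

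**Working it through.** **The plan's own figure.** The Sample size section gives 6 to 13 participants for effect sizes 2.4 to 0.9, two-tailed alpha 0.05 and power 0.8. It names no test. A paired t-test needs 4 and 12, so both ends agree to within two participants. With 16 participants and effect size 0.9, the power of that test is 92%. The 80% used below is therefore a common reference point and not a forecast for this trial.

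**Inputs.** From the article: 16 participants, 3 conditions, 2 times, so 16 × 3 × 2 = 96 values per outcome. Assumed: complete data, no period effects, and a correlation ρ between pre and post at the same visit, given subject. The documents give no value for ρ, so a range is shown. Equivalently, the visit variance is v = ρ/(1 − ρ) times the residual variance.

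**Expected residual under the stated model.** Scale visit plus residual variance to 1. After removal of subjects and the fixed effects, 96 − 16 − 5 = 75 degrees of freedom remain:

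- subject by condition: 15 × 2 = 30, expected mean square (1 − ρ) + 2ρ = 1 + ρ;
- subject by time (15) and subject by time by condition (30): 45 in all, expected mean square 1 − ρ.

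The subject-only model pools them. REML divides the sum of squares by 75 and ML by 96 − 16 = 80. The correct variance for the time-by-condition contrast is 1 − ρ, because the visit effect cancels. Hence, under ML,

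SE ratio = √{[30(1 + ρ) + 45(1 − ρ)] / [80(1 − ρ)]} = √{(75 − 15ρ) / [80(1 − ρ)]}.

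Power, for an effect that the correct SE would detect with 80% probability (effect/SE = 2.8), is Φ(2.8 − 1.96 × ratio).

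| ρ | SE ratio (ML) | Power |
|---|---|---|
| 0 | 0.968 | 82% |
| 0.1 | 1.01 | 79% |
| 0.2 | 1.06 | 77% (rounded up from 76.5%) |
| 0.33 | 1.14 | 71% |
| 0.5 | 1.30 | 60% |

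Simulated type I error of the subject-only ML model with a normal reference is 4.3%, 2.9% and 1.4% at v = 0.25, 0.5 and 1 (ρ = 0.2, 0.33 and 0.5). With a visit effect, REML and t on 45 degrees of freedom it is 4.8% to 5.2%.

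**ML alone.** With ρ = 0 the ratio is √(75/80) = 0.968, so SEs are about 3% too small. With a visit effect in the model it is √(45/48), the same value. Type I error is then about 5.8% with a t reference and 6.2% to 6.4% with a normal one (75 and 45 degrees of freedom), if the covariance is otherwise right.

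**Direction.** The two effects oppose each other. They cancel where 75 − 15ρ = 80 − 80ρ, so ρ = 5/65 = 0.077.

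**Within-condition tests.** Suppose participants also differ in their pre-post change. Let a subject-by-time variance s, relative to a residual variance of 1, give the change a variance of 2(1 + s). Under ML the SE ratio for a within-condition change is √{(75 + 60v + 45s) / [80(1 + s)]}. With s = 0.5 and v = 0 this is √(97.5/120) = 0.90, and the simulated type I error is 8.2%. With s = 0.5 it reaches 1 when 60v = 120 − 97.5, so v = 0.375. At v = 0.5 it is √(127.5/120) = 1.03, which is already conservative.

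**The case against.** The strongest reply is that the article nowhere says subject is the sole random effect. A journal article condenses the plan, and nested terms, covariance structure and degrees of freedom often belong in an analysis plan that is not shown here. This stands as far as silence goes. But the article does make choices: it names the random effect for the primary and again for the secondary outcomes, and it names the estimator with a reason. Those choices can be judged against the design.

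A second reply is that shared day variance may be small for the primary outcome. Oxy-Hb is analysed as 2-back or 3-back against 1-back within one assessment, so an additive day shift drops out beforehand. The Discussion mentions repositioning of the cap between pre-test and post-test, and the system is calibrated before each assessment. Matched dinners, repeated breakfasts, taxi transport and a consistent weekday also reduce day-to-day variation. All of this stands and points to the lower rows of ρ for oxy-Hb. It has less force for mood, alertness, sleepiness, cortisol and reaction time, which are analysed with the same model.

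A reader might infer more than the documents support, in two ways:

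- That the standard errors are simply wrong. They depend on an unreported correlation, are about right near 0.08, and the ML effect offsets the other.
- That the interaction test is too conservative while within-condition tests are clearly too liberal. The 8.2% above arises with no visit variance; at visit variances large enough to widen the interaction SE materially through the missing visit term, the within-condition excess disappears.

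Finally, the article's statement that likelihood estimation copes with data missing at random is correct. It just does not favour ML over REML.

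**Conclusion.** The point holds in a limited form. Read as written, the model ignores the pairing of pre and post within a visit. If the within-visit correlation is appreciable, the time-by-condition test is conservative and loses power: little at 0.1, and about 9 percentage points (80% to 71%) at 0.33 and 20 (80% to 60%) at 0.5. This is a loss of efficiency, not a bias in the estimated effects. The ML understatement of about 3% is minor and avoidable, and it partly offsets the first effect. Apart from that 3%, within-condition tests become too liberal only if participants differ in their change and visit variance is small. All sizes rest on an assumed correlation, complete balanced data and no period effects. The change is worth making because it costs so little.

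**What to change.** State a random effect for visit within subject (equivalently subject by condition) in the primary and secondary models, or analyse the within-visit changes. Add a subject-by-time random effect only if it can be estimated. Fit by REML with Kenward-Roger degrees of freedom, and say that data missing at random are handled by this likelihood.

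This changes the specification only. If the visit variance is estimated as zero, the model falls back almost to the stated one. With a visit term the interaction test rests on about 45 instead of 75 degrees of freedom, a small price. Change scores are simpler but drop any visit with only one of its two values, so the mixed model is preferable if such visits occur.
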